### Healthcare cost and utilisation

Healthcare cost consists of the total cost incurred for providing care. It includes the relevant labour, medication, room, service and administrative costs prior to any form of subsidies or reimbursement. The aggregate cost and utilisation 1 year prior to recruitment will be taken as the baseline and compared with the aggregate cost and utilisation between the first to the second annual review.

Total healthcare cost will be examined for both polyclinic and overall hospital care utilisation from relevant EMRs or billing record systems. Cost data will be standardised to a full year for fair comparison. Change in healthcare cost between Intervention and Control will be modelled using generalised linear regression with log-link and gamma distribution or difference-in-difference analysis with covariate adjustment. Healthcare utilisation (polyclinic attendance, SOC, emergency departments, hospital admissions), which are positive count data, will be modelled using Poisson or zero inflated negative binomial regression adjusting for covariates following preliminary analysis [34].

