### Secondary outcomes

Secondary outcomes will be compared between patients receiving the CSP intervention with patients receiving standard care, from baseline to study endpoint.

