#### Healthcare Services Utilisation and Cost

Change in healthcare utilisation in terms of number of polyclinic, emergency department, hospital admissions and SOC visits from one year preceding recruitment to the period between the first and the second annual reviewChange in healthcare cost in terms of total healthcare cost from polyclinic, emergency department, hospital admissions and SOC visits from one year preceding the first annual review to the period between the first and the second annual review

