## Sample size calculation

The sample size calculation was based on HbA1c, the primary outcome measure, for which a difference of 0.5 percentage points was taken to be clinically meaningful. The sample size of 1620 was calculated based on 1:1 allocation into the Intervention and Control, 6 pre-specified subgroups (with 3 age tertiles and 2 gender groups), at a power of 90%, with an alpha value of 0.05 (95% confidence interval) and accounting for an attrition rate of 30%. The study team aims to recruit a total of 1620 patients across the four sites.

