## Statistical methods

### Statistical analyses

Descriptive statistics of the baseline data will be reported, and exploratory data analysis will be conducted prior to model building. Continuous variables will first be tested for normality of distribution. Bivariate analyses will be conducted for continuous variables, and chi-squared test or Fisher’s exact test for categorical variables will be used to determine statistically significant differences between the Intervention and the Control for each baseline characteristic. The analysis will be conducted with the intention-to-treat (ITT) principle unless otherwise specified. Missing endpoints will be imputed with the last observation carried forward (LOCF).

Generalised linear regression will be used to analyse the study endpoint (HbA1c) and while controlling for baseline HbA1c as a covariate. PAM-13 score and other secondary continuous outcomes variables will follow the same analysis methods unless otherwise stated. Logistic regression will be utilised to assess binary outcomes such as screening compliance in the past year, smoking status, and frequent exercise status. Covariates and interaction terms to be included in the model will be selected through inquiry of the data and reviewing existing literature. A stepwise process will be used to drop covariates that have a *p*-value greater than or equal to 0.2. Akaike information criterion (AIC) will be used to decide on the linear model used for potentially non-normal dependent variables such as total cost. Covariates included in the various models will be reported. The outcomes will be compared between the Intervention and the Control. Statistical tests will be conducted at a 2-sided alpha level of 0.05 with confidence intervals calculated at 95%, 2-sided unless otherwise stated. All analysis will be conducted using the STATA software version 16.

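### Visit counts: the two models offered, chosen after preliminary analysis, have arm coefficients that estimate different things, and the ratio of mean visits is not fixed as the contrast

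*Protocol article*

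**What the plan says.** Utilisation is a secondary outcome. Under Healthcare Services Utilisation and Cost it is defined as "Change in healthcare utilisation in terms of number of polyclinic, emergency department, hospital admissions and SOC visits", from the year before recruitment to the interval between the two annual reviews. The Secondary outcomes section sets the comparison: "Secondary outcomes will be compared between patients receiving the CSP intervention with patients receiving standard care, from baseline to study endpoint". The quantity of interest is therefore how many visits patients make, by arm.

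The analysis is in the healthcare cost and utilisation section under Statistical methods. It says the four visit types, "which are positive count data, will be modelled using Poisson or zero inflated negative binomial regression adjusting for covariates following preliminary analysis". Ordinary negative binomial regression, a robust variance and a marginal-mean contrast are not named, and no rule is given for choosing between the two models. The Statistical analyses section adds that "Statistical tests will be conducted at a 2-sided alpha level of 0.05" and describes a stepwise process that removes covariates with p of 0.2 or more. The AIC rule there is given for linear models of outcomes such as total cost, not for counts.

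**The concern.** Each named model, used in its ordinary form, has a known weakness for this outcome.

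- **Poisson.** The arm coefficient is the log ratio of mean visits, which is the right target. Its default standard error assumes that the variance equals the mean. The article's account of current diabetes care ties the number of interim reviews to each patient's condition and control, so visit rates should differ between patients and the counts should be overdispersed.
- **Zero-inflated negative binomial.** The count coefficient compares visit rates among latent potential users. Patients kept out of hospital altogether act on the zero part, which that coefficient does not measure. Conversely, it can differ between arms when mean visits are the same.

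Because the choice follows preliminary analysis, what the reported arm effect means could depend on the data. The plan also goes straight from Poisson to a zero-inflated model, without the usual intermediate model for overdispersed counts. That gap is most visible for polyclinic attendance: every participant is under a teamlet with scheduled reviews, so a class of structural non-attenders is hard to picture.

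At stake is the utilisation comparison, part of a secondary objective that the article links to health policy interest. It could give too many false positives, or an arm effect that is not about mean visits.

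**Working it through.** **Inputs from the article.** Two-sided alpha is 0.05. On recruitment, "The study team aims to recruit a total of 1620 patients across the four sites", with 1:1 allocation and 30% attrition. Completers: 1620 × 0.70 = 1134, or 567 per arm. The 1620 was calculated for HbA1c. The article gives no visit rate, dispersion, share of non-users or power for utilisation, so there is no utilisation figure to reproduce. Everything below on rates and dispersion is assumed.

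**Step 1: size of the default Poisson test.** With φ = variance/mean, the model-based standard error is too small by a factor √φ, so

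size = 2 × [1 − Φ(1.96/√φ)].

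| φ (assumed) | 1.96/√φ | True size |
|---|---|---|
| 1 | 1.960 | 0.050 |
| 1.25 | 1.753 | 0.080 |
| 1.5 | 1.600 | 0.110 |
| 2 | 1.386 | 0.166 |
| 3 | 1.132 | 0.258 |

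The size reaches twice nominal at φ = (1.96/1.645)² ≈ 1.42. The formula does not depend on the sample size.

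Simulated gamma-Poisson counts (567 per arm, 4000 runs per setting, means from 0.2 to 5 visits, no covariates) agree:

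- default standard errors: 0.115–0.125 at φ = 1.6, 0.158–0.168 at 2 and 0.259–0.263 at 3;
- robust standard errors: 0.047–0.057 in all eight settings.

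**Step 2: would Poisson survive preliminary analysis?** A Pearson dispersion check, which the article does not specify, kept Poisson in 0% of runs at φ of 1.6 or more. At φ = 1.2 it kept Poisson in 2.8%, and the size among those was 0.045. If such a check is made, the usual path leads to the zero-inflated model.

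**Step 3: what the zero-inflated count coefficient tests.** Let π be the structural-zero share and μ the mean among potential users, so that

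mean visits = (1 − π) × μ.

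Assumed control arm: π = 0.40, μ = 2, mean 0.60 × 2 = 1.2; negative binomial dispersion 0.5; 567 per arm; 600 runs per scenario.

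| Intervention arm | Mean | Count coefficient rejects | Marginal mean ratio rejects |
|---|---|---|---|
| Identical to control | 1.2 | 7.2% | 4.7% |
| π = 0.55, μ = 2 (effect only in zeros) | 0.45 × 2 = 0.9 | 4.8% | 83% |
| π = 0.55, μ = 2.667 (equal means) | 0.45 × 2.667 = 1.2 | 85% | 4.8% |
| π = 0.40, μ = 1.5 (effect only in count) | 0.60 × 1.5 = 0.9 | 81% | 87% |

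The count coefficient performs well only in the last row. The marginal ratio from the same fitted model performs well in all four. Poisson with robust standard errors gives almost the same rejection rates as the marginal ratio: 4.7%, 83%, 4.8% and 87%.

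**The case against.** The strongest reply is that the article names model families and nothing more. It does not say that Poisson will be run with default standard errors, or that the zero-inflated count coefficient will be the test. Variance type and reported contrast are often left to an analysis plan, and none is shown. The choice is also conditional, and Step 2 shows that a simple check would rarely leave Poisson in place when it matters. Covariate adjustment may reduce residual overdispersion. A zero-inflated negative binomial approaches the ordinary one as the zero inflation vanishes. The scenario with the whole effect in the zeros is constructed; the article does not say that the programme acts that way.

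Most of this stands as a limit on the size of the problem. It also rules out a stronger reading that a reader might infer: that neither model tests equal mean utilisation, so the result must be either anti-conservative or blind to avoided use. The documents do not support that. The Poisson coefficient is the log ratio of means and only its default error fails. A zero-inflated fit yields a valid marginal mean ratio.

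Calling the counts positive is at most loose wording, since the same sentence allows for excess zeros.

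What the reply does not remove is what the article itself fixes: a menu of two models whose ordinary arm effects differ in meaning, a choice made after looking at the data, and no ordinary negative binomial among the options.

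**Conclusion.** The point holds in limited form. The plan offers two count models with different default targets, chooses between them after preliminary analysis, and does not fix the between-arm contrast as the ratio of mean visits.

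If Poisson were kept with default errors, the false-positive rate would be about 11% at a variance-to-mean ratio of 1.5 and 17% at 2. If the zero-inflated count coefficient were reported as the arm effect, it could miss a 25% fall in mean visits that lies in the zeros (1.2 to 0.9), or reject when the means are equal.

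These figures rest on assumed rates, dispersion and zero shares, 567 independent patients per arm and no covariates. They show what could happen under the wording, not what will. The outcome is secondary, and the HbA1c analysis is unaffected.

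**What to change.** In the healthcare cost and utilisation section under Statistical methods, replace the choice of models with a statement along these lines: for each visit type, the between-arm contrast is the ratio of mean visits, estimated from a log-link count model (Poisson with robust standard errors, or ordinary negative binomial; name one). The patient's baseline-year count is always kept as a covariate and is exempt from stepwise removal. If a zero-inflated model is used, its marginal mean ratio is reported, not the count coefficient.

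Keeping the baseline count matters because the arms are not randomised and the outcome is defined as a change. The count is already to be collected.

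The cost is a change of wording, and these are standard methods in statistical software. Intervals will be wider than ordinary Poisson would give.

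The change should not be presented as making the intervals fully valid. There are two clinics per arm with one participating teamlet each, and patient-level robust errors do not cover variation between clinics.

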## Dissemination policy

Findings from the study will be disseminated through presentations at international conferences, publications in medical journals or other media platforms. They will also be communicated to the Singapore Ministry of Health and other key stakeholders of the project.

## Discussion

PACE-D evaluates the effectiveness of personalised CSP in persons living with diabetes. The multi-pronged programme aims to help patients prepare for their consultation, to participate collaboratively in discussions about their goals and how they might pursue them, and to facilitate their participation in community programmes that support self-management. The interventions in the programme leverage the strengths of the existing team-based care model adopted in the polyclinics that is intended to allow better relationship to be built between patients and their care team, to improve patient experience, and possibly to improve clinical outcomes. In addition, this trial is unique in that the CSPs are practised in the multicultural and multilingual Singapore primary care setting – CSPs are conducted in the English, Malay and/or Chinese language depending on the language proficiencies of the enrolled patients and the CSP practitioners.

In designing and implementing this complex trial which entails measuring and evaluating outcomes across the intervention and control groups over pre- and post- interventions, a number of challenges in wide-ranging areas have been encountered. They include the transfer of knowledge and skills of the UK YoC Partnerships care model to a local core team of doctors and nurses accredited as qualified local trainers in Singapore; adapting the training materials to the local primary care context by the accredited local trainers who went on to conduct training for the CSP practitioners; developing technical and computer skills to operationalise the preparation of CPLs; and integrating CSP conversations as part of routine care that require additional consultation time from the CSP practitioners.

While the one-two year timeline may be adequate to see initial improvements in clinical outcomes, the duration may not be long enough for the full effects of the CSP model of care to be observed or understood. Nonetheless, the key strength of PACE-D is that this is a pragmatic trial conducted in routine primary care practices where HCPs have to grapple with a scarcity of time and resources to deliver holistic care to patients with LTCs. Successful implementation of the programme therefore affirms the new care model is feasible in real world non-study settings and supports greater generalisability of the study findings for other primary care practices. This study will increase understanding of the role of personalised CSPs in the delivery of care for persons living with diabetes.

## Data Availability

Not applicable.

## Abbreviations

AR: Annual Review
BI: Business Intelligence
CC: Care Coordinator
CM: Care Manager
CSP: Care and Support Planning
CPL: Care Planning Letter
ePOS: Electronic Polyclinic Outpatient System
EMR: Electronic Medical Record
HbA1c: Glycated Haemoglobin
HCP: Health Care Provider
ITT: Intention-to-treat
LOCF: Last Observation Carried Forward
LTC: Long Term Condition
MOH: Ministry of Health
NUP: National University Polyclinics
NUHS: National University Health System
PACE-D: Patient Activation through Community Empowerment/Engagement for Diabetes Management
PAM-13: Patient Activation Measure-13
PC: PACE-D Coordinator
PCP: Primary Care Physician
SGD: Singapore Dollar
SOC: Specialist Outpatient Clinic
UK: United Kingdom
YoC: Year of Care
